30. Revision History................................................................................................................................ 27

List of abbreviations

| abbreviation | Unabbreviated Expression (English) | Unabbreviated expressions (Japanese) |
| --- | --- | --- |
| FLACC | Face, Legs, Activity, Cry, Consolability Scale | no translation into Japanese |

1. Outline of Clinical Research

| Objective. | Exploring the pain-relieving effects and safety of TAK-01 when injected subcutaneously in young children |
| --- | --- |
| Test Equipment | TAK-01 (cooling pack) |
| Research Design | Multicenter, two-arm, single-blind, randomized, parallel-group study |
| person who is being studied | Preschool children aged 3 to 6 at the time of obtaining consent to receive immunization by subcutaneous injection |
| Primary Endpoint | FLACC scale evaluation by FLACC scale evaluation committee members after immunization implementation |
| secondary endpoint | FLACC scale evaluation after immunization by attendant  Incidence of Adverse Events |
| Eligibility Criteria | Selection Criteria] The following criteria are all met at the time of case enrollment.   1. Preschool children aged 3 to 6 years at the time of case enrollment 2. Those scheduled to receive subcutaneous Japanese encephalitis vaccine or influenza vaccine at the time of case enrollment. 3. A person who has obtained the free and voluntary written consent of a surrogate to participate in this study.   Exclusion Criteria] Patients who meet at least one of the following criteria at the time of case registration are eligible  Exclude as   1. Those who are chirping more intensely than before consent was obtained. 2. Persons with sensory insensitivity or intellectual disability at the time of obtaining consent 3. Persons scheduled to receive two or more vaccinations on the date consent is obtained 4. Who used analgesics within 6 hours prior to case enrollment 5. Persons diagnosed with or suspected of having a cold-stimulus-related illness such as Raynaud's syndrome or sickle cell disease at the time consent is obtained   (6) Persons who are judged by the principal investigator (subinvestigator) to be inappropriate to participate in this study |
| Observation Schedule | Obtain consent, assign, and use the test device (hereafter referred to as TAK-01) at the time of vaccination outpatient visit, and observe until 10 minutes after the vaccination is administered. |
| Target number of cases | 60 cases (30 in cooling group, 30 in non-cooling group) |
| Scheduled implementation period | April 2021 - September 2022  (Patient enrollment period: jRCT release date to March 2022) |

#

2. Background

Medical procedures on children, including injections, typically cause pain and distress. Relieving pain during medical procedures promotes a positive attitude toward later medical care(1) . According to evidence-based clinical practice guidelines, a combination of pharmacologic, physical, and psychological approaches is effective in reducing pain in children from immunizations(2) (3) (4) (4) (5) (6) (7) (8) (9)

A network meta-analysis of randomized controlled trials examining the effect of pharmacological interventions on vaccine pain relief in children concluded that topical application of a lidocaine and procaine eutectic mixture cream formulation (Emla Cream®) significantly relieved pain, although the level of evidence was insufficient(4) . In one of the studies examined in this analysis, a double-blind, randomized, controlled trial of the pain-relieving effect of Emla Cream® at the time of vaccination in young children (4-6 years), using the affected children's own face pain scale (0 = no pain, 6 = maximum pain on a 7-point scale), the intervention group (n = 83, median 1.3 , SD 1.87) showed significantly greater pain relief than the placebo group (n=76, median 2.3, SD 2.31) (p=0.02)(5). In Japan, Hanaoka et al. studied the local anesthetic effect of Emla cream at the time of venipuncture in adults, but not in adults between 20 and 65 years of age, in a multicenter, placebo-controlled, randomized, double-blind, parallel-group study with the Visual Analogue Scale (VAS) of pain as the primary endpoint showed a significant local anesthetic effect in the intervention group (n=42, median 18.88 mm, SD 17.36) compared to the placebo group (n=44, median 39.6 mm, SD 22.94) (p < 0.001).(6) .

The World Health Organization's position paper on pain relief at the time of vaccination considers interests, values and preferences of the vaccinated, resource utilization, intervention costs, equity implications, acceptability, and feasibility from a global perspective, and outlines the following four policies(7). The following four policies have been identified in consideration of the value of the individual being vaccinated: (i)  Health-care personnel carrying out vaccination should be calm, collaborative and well informed; they should use neutral words (e.g. “here I go” rather than “here comes the sting”) and avoid language that increases anxiety, promotes distrust and/or is falsely reassuring or dishonest (e.g. phrases such as “it will only hurt for a second”). (ii)  Proper positioning of the vaccine recipient should be ensured, according to age.8 Holding by the care- giver is recommended for infants and young children, and sitting upright for older populations. Lying down may be preferred for those with a history of fainting. (iii)  No aspiration should be done during intramuscular injections, as this may increase pain due to longer contact time and lateral movement of the needle. (iv) When multiple vaccines are injected sequentially in the same session they should be administered in order of increasing painfulness. The following four special considerations should be made for children:(i) The caregiver should be present throughout and after the vaccination procedure. (ii)  Infants and children aged <3 years should be held by caregivers throughout the procedure, and those aged ≥3 years should be seated to alleviate fear and distress, preferably on the caregiver’s lap. (iii)  If culturally acceptable, breastfeeding of infants should be done during or shortly before the vaccination session.11 Where oral vaccines are being co-administered with injectable vaccines, it would be best to proceed with the administration of oral rotavirus vaccine, then oral polio vaccine (if OPV is used), then breastfeeding with simultaneous administration of the injectable vaccines. (iv)  For children <6 years of age, distractions to divert attention away from pain to something more pleas- ant (e.g. with toys, video, music, or conversation with an adult) are recommended. In our country, pharmacological interventions are rarely used at the time of vaccination, although there are opportunities to use them for planned procedures for chronically ill pediatric patients. In fact, the accompanying dosage and administration of Emla Cream® states that the cream should be applied 60 minutes before the procedure is performed, which takes time for the effect to develop.

On the other hand, skin cooling has been used for centuries to relieve pain. Skin cooling is characterized by its rapid onset of pain relief, simplicity, cost-effectiveness, and virtually no side effects. The pain-relieving effect of skin cooling begins to appear at a skin temperature of 10°C and increases as the temperature approaches 0°C. The analgesic effect is also enhanced by the suppression of autonomic nervous system responses due to the decrease in skin conductivity and skin blood flow caused by cooling. In actual clinical practice, we have been cooling the inoculation site before inoculation for infants who refuse subcutaneous injections because they complain of pain from subcutaneous injections. We have had many cases in which infants who refused subcutaneous injections were well accepted, and we were able to elicit a positive attitude toward subcutaneous injections. Initially, ice packs were made by filling medical gloves with ice water, but since several years ago, we have been using "PuruCURE Ice Pack®," a cooling pack manufactured and marketed by Mie Chemical Industry Co. However, a systematic review of the pain-relieving effects of vaccination site skin cooling has shown that it is effective in adults, but no conclusion can be drawn at this time for children(8) . The reasons for this may include the fact that children are less expressive of their emotions than adults, and that in many papers, the pain assessors are not the patients themselves but their parents or guardians. Therefore, we decided to investigate the pain-relieving effects and safety of TAK-01 during subcutaneous injection for infants by having the currently marketed "PuruCURE Icepack®" manufactured in a smaller size that is easier to apply to infants' upper arms to improve convenience.

3. Objective

Exploring the pain-relieving effects and safety of TAK-01 when injected subcutaneously in young children

4. Outline of TAK-01

4.1 TAK-01 shape, structure and principle

　 Structure

[figure not shown]

[figure not shown]

　　Coolant contents (gel) Crystal Gel®* (gel)

*Crystal Gel® will be used by Tanac Corporation, and Mie Chemical Co., Ltd. will handle the rest of the sales, including filling of coolant contents.

[figure not shown]
Shape

**95 mm**

**135 mm**

The size of about 95 mm x 270 mm is called "Puru CURE Icepack®" and is sold under the trade name "Puru CURE Icepack®.

Notified as a general medical device by Mie Chemical Industry Co.

Classification: Instrument 12 Physiotherapy equipment General name: Cooling pack (Code: 37240020)

　　　Principle

　　　　　This product containing a cooling medium is cooled and stored in a cooling device, and the cooling effect is used to cool the affected area.

Cooling

4.1.2 TAK-01 providers

Mie Chemical Industry Co.

4.2 Anticipated diseases, etc.

Frostbite, etc. when used directly against the skin.

4.3 Anticipated Defects

Damage due to excessive load

5. Research Subjects

5.1 Selection Criteria

The study will include those who meet all of the following criteria at the time of case enrollment

1. Preschool children aged 3 to 6 years at the time of case enrollment
2. Those scheduled to receive subcutaneous Japanese encephalitis or influenza vaccination at the time of case enrollment.
3. A person who has obtained the free and voluntary written consent of a surrogate to participate in this study.

Basis for setting

　(1) Provisions pertaining to the subject of this study, in order to reduce the risk of a blind split.

　(2) For regulations pertaining to the subject of this research

(3) To protect research subjects

5.2 Exclusion Criteria

At the time of case enrollment, patients with any one of the following conditions will be excluded from the study

1. Those who have been chirping violently since before consent was obtained
2. Persons with sensory insensitivity or intellectual disability at the time of obtaining consent
3. Persons who are scheduled to receive two or more vaccinations on the date consent is obtained
4. Who used analgesics within 6 hours prior to case registration
5. Persons who have been diagnosed or are suspected of having been diagnosed Raynaud's syndrome, sickle cell disease or cold stimulus-related disease at the time consent is obtained
6. Persons who are judged by the principal investigator (or subinvestigator) to be inappropriate to participate in this study.

Basis for setting

1. If the subject is crying violently, there is a high possibility that the local cooling with TAK-01 itself will be rejected and the study will not be completed.
2. (3)(5)(6) To influence the endpoints and to ensure the safety of research subjects

(4) To affect the evaluation items

(6) To ensure the safety of research subjects

6. Clinical Research Methods

- 1. Research Design Overview

6.1.1 Types and Methods of Clinical Research

Multicenter, single-blind, blind assessment, randomized (allocation factor: institution), two-parallel group comparison

6.1.2 Explanation of the relevance of the study design

　　The study was multicenter and single-blind because the technique of pressing TAK-01 to the injection site makes it difficult to blind the investigators.

　Although applying a cooling pack to the vaccination site is not a standard treatment, the comparison was made between the cooling group and the non-cooling group, rather than between the TAK-01 use group and the non-use group, in order to blind the attendants and the FLACC scale evaluation committee members who were to conduct the FLACC scale evaluation.

　Although it is possible that the 　study subjects themselves could be blinded, the age range was limited to 3-6 years to reduce the risk of such a split, and a blind assessment method by the FLACC scale assessors was used for the primary assessment.

　Because the immunization procedure is also considered a pain factor, the facility was used as an allocation factor to divide the patients into two groups within the facility: a cooling group and a noncooling group.

6.1.3 Duration of subject's participation in the study and observation period

　10 minutes from obtaining　consent to completion of immunization

<Schema: Figure 1>

[figure not shown]

6.2 Registration

6.2.1 Registration Method

　　After explaining this study in writing when the patient comes to the hospital for immunization, the proxy consents to the study.

Registration shall be made upon obtaining and signing the consent form.

6.2.2 Method of Randomization

　After consent is obtained, the investigators at the implementing institution will randomly assign the facility as the allocation factor using the REDCap system.

6.2.3 Blinding procedure

　 The study will be single-blind, with the staff of the implementing medical institution being unblinded and the study subjects and attendants being blinded.

6.3 Research Plan Treatment

　Cooling group: TAK-01 is cooled for at least 3 hours in a freezer (internal temperature: -16 to -20 degrees C), removed from the freezer, and allowed to permeate for 1 to 3 hours in ice water. The TAK-01 is then applied directly to the subject's vaccination site for 30-60 seconds, and inoculation is performed within 1 minute after the TAK-01 is removed.

　Uncooled group: TAK-01 is placed at room temperature (approximately 20 degrees Celsius) for at least 3 hours, and is applied directly to the subject's vaccination site for 30 to 60 seconds.

6.4 Concomitant medications/adjunctive therapy

　Concomitant therapy and concomitant medications

None in particular.

　　 Prohibited concomitant medications and prohibited concomitant therapies

　　　The following concomitant medications/adjunctive therapies are not performed due to their strong impact on the FLACC scale assessment.

　　　　　Prohibited concomitant medications: administration of analgesics and sedatives at the time of vaccination and local anesthesia at the vaccination site.

Concomitant Prohibited Therapy: showing videos or other actions to distract from injections during immunization

6.5 Criteria for Discontinuation of Research Protocol Treatment

If you are unable to receive the vaccination after obtaining consent.

If the TAK-01 is not available to the research subject, or if the time to apply the TAK-01 is less than 30 seconds.

If the vaccination could not be administered within 1 minute after the TAK-01 was removed.

When it is difficult to observe as prescribed due to adverse events, etc.

When the principal investigator decides to discontinue the study

However, for study subjects using TAK-01, in addition to the 10-minute post-immunization observation, the FLACC scale evaluation will be performed immediately after immunization by an attendant and later by the FLACC scale evaluator after viewing the imaged video.

6.6 TAK-01 Administration and Delivery Procedures

　 TAK-01 should be stored in a secure area and kept separate from other equipment.

Details are set forth in the "Test Equipment Management Procedures".

7. Assessment Items

7.2 Secondary endpoints

　FLACC scale evaluation after immunization by attendant

Incidence of Adverse Events

7.3 Judging Criteria

FLACC scale

[figure not shown]
8. Observation and examination items

Schedule Overview

After obtaining written consent from the proxy on the day of vaccination, registration and allocation will be conducted for outpatient immunization recipients of the relevant age group.

Video recording from before TAK-01 use to 10 seconds after inoculation.

The detailed imaging procedures for moving images are set forth in the "Procedures for Imaging".

After vaccination, the FLACC scale was evaluated by an attendant.

The video will be reviewed by the FLACC scale evaluation committee members at a later date and the FLACC scale evaluation will be performed.

The evaluation procedure by the scale evaluation committee members is described in the "Procedures for the Work of the FLACC Scale Evaluation Committee Members".

The following is set forth in Section 2.1.1.

|  | During Outpatient Consultations  Consent/Registration | Before inoculation | vaccination | 10 minutes after inoculation | time of discontinuance |
| --- | --- | --- | --- | --- | --- |
| Basic Information |  |  |  |  |  |
| agreement |  |  |  |  |  |
| Registration and allocation |  |  |  |  |  |
| Video Shooting |  |  |  | ^＊１^ |  |
| Using TAK-01^＊2^ |  |  |  |  |  |
| Immunization Practice^*3^ |  |  |  |  |  |
| FLACC evaluation (by attendant) |  |  |  |  |  |
| adverse event^＊4^ |  |  | | |  |
| Diseases, etc.^＊5^ |  |  |  |  |  |

*1 Movie will be taken 10 seconds before TAK-01 use and after inoculation.

*2 Press the assigned TAK-01 directly on the injection vaccination site for 30-60 seconds

*3 Perform within 1 minute after the end of TAK-01 use.

*4 Adverse events: Collect from the start of application of TAK-01 to 10 minutes after inoculation.

*5 Diseases, etc.: Collect events for which a causal relationship with TAK-01 cannot be ruled out from the start of TAK-01 application to 10 minutes after inoculation.

8.1 During an outpatient visit

8.1.1 Collection of basic information

　　Age, Gender, Types of vaccinations and Blunted sensory perception

8.2 Obtaining Consent and Confirming Eligibility

Obtain written consent from the surrogate and confirm eligibility with the eligibility form.

8.3 allocation

　　Once the eligibility is confirmed on the Eligibility Verification Form, the registration and assignment process is performed in the REDCap system.

8.4 Before inoculation

Started taking video before using TAK-01

Use of TAK-01 in assigned groups

Adverse events, diseases, etc. (collected from the point of use of TAK-01)

8.5 Immunization

　　Collection of adverse events, diseases, etc.

　　　However, adverse events that can be clearly attributed to immunization are not included in the collection.

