8.6 After inoculation

　　Video recording ends after 10 seconds of inoculation

　　FLACC scale evaluation by attendant

　　Collect adverse events, diseases, etc. up to 10 minutes after vaccination

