10.1 Definition of adverse events

All unfavorable events or unintended illnesses or signs of illness (including abnormal laboratory values) that occur in research subjects using TAK-01. This refers to all unfavorable events or unintended illnesses or signs of illness (including abnormalities in clinical laboratory values) that occur in research subjects using TAK-01, regardless of whether they are causally related to this study.

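### The section 8.5 exception for events clearly due to immunization contradicts the causality-free adverse event definition and can distort or hide arm differences in local reactions

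*Protocol*

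**What the plan says.** Five parts of the protocol bear on which adverse events reach the case report form.

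- **Definition (10.1).** All unfavourable events in children using TAK-01 count, "regardless of whether they are causally related to this study". Both arms use TAK-01, cooled or at room temperature, so the definition covers both.
- **Schedule note *4 (section 8).** "Adverse events: Collect from the start of application of TAK-01 to 10 minutes after inoculation". There is no exception by cause.
- **Immunization step (8.5).** "However, adverse events that can be clearly attributed to immunization are not included in the collection".
- **After inoculation (8.6).** "Collect adverse events, diseases, etc. up to 10 minutes after vaccination". Again there is no exception.
- **Serious events (10.2.1).** These are reported whether or not they are related.

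Section 7.2 makes "Incidence of Adverse Events" a secondary endpoint. Section 14.4.3 summarises it with counts and percentages, then tabulates device-related events in the same way. Section 6.2.3 describes the trial as single-blind, "with the staff of the implementing medical institution being unblinded and the study subjects and attendants being blinded".

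**The concern.** An event defined without regard to cause cannot also be left out because of its cause. Two sites could treat the same reaction differently, and each could point to a section that supports it.

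The filter matters more here than in most trials because the device and the vaccine share a site and a time. In the cooling group the pack is held on the "vaccination site for 30-60 seconds, and inoculation is performed within 1 minute after the TAK-01 is removed", and note *3 applies the one-minute limit without distinguishing the arms. The anticipated harm of the device is itself local: "Frostbite, etc. when used directly against the skin". Redness or swelling at that spot could come from either source, and whoever decides probably knows whether the pack was cold.

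Safety is half of the stated objective, and adverse event incidence is the only safety endpoint. A non-serious event left off the form cannot be restored by any later analysis, so this cannot be left to a statistical analysis plan.

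**Working it through.** **1. The texts side by side.**

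| Place | Period | Exception by cause |
|---|---|---|
| 10.1 | use of TAK-01 | none; cause is expressly irrelevant |
| Note *4 | start of application to 10 minutes after inoculation | none |
| 8.4 | from use of TAK-01 | none |
| 8.5 | immunization step | events clearly due to immunization left out |
| 8.6 | to 10 minutes after vaccination | none |
| 10.2.1 | serious events | none; reported regardless of relationship |

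Section 8.5 stands alone. It does not say whether its exception reaches into the 10 minutes that 8.6 covers. The protocol gives no criterion for *clearly*, no blinded attribution and no log of what is left out.

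**2. Who attributes.** Section 8.5 does not say. Section 16.1 has the investigators complete the case report form, and 6.2.3 leaves site staff unblinded. That the judgement is made with knowledge of the arm is therefore an inference, though a natural one.

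**3. What a filter does to the recorded rate.** The protocol states no adverse event rate, so there is no figure to reproduce. The rates and exclusion shares below are assumptions; only the 30 children per arm come from the document (14.2). Let *p* be the true rate and *e* the share of events left out as due to the vaccine. Then

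recorded rate = p × (1 − e).

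If *p* is the same in both arms, the recorded difference (cooling minus non-cooling) is p × (e_non-cooling − e_cooling). With e = 0.40 in the cooling arm and e = 0.80 in the non-cooling arm:

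| True rate, both arms | Recorded, cooling | Recorded, non-cooling | Spurious difference | Expected children of 30 |
|---|---|---|---|---|
| 10% | 0.10 × 0.60 = 6% | 0.10 × 0.20 = 2% | +4 points | 1.8 v 0.6 |
| 30% | 0.30 × 0.60 = 18% | 0.30 × 0.20 = 6% | +12 points | 5.4 v 1.8 |
| 50% | 0.50 × 0.60 = 30% | 0.50 × 0.20 = 10% | +20 points | 9.0 v 3.0 |

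Swapping the two shares gives −4, −12 and −20 points.

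**4. Equal exclusion in both arms.** No false difference arises, but a real one shrinks. Take true rates of 30% and 10%, a difference of 20 points:

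- e = 0.50 in both arms: 15% − 5% = 10 points.
- e = 0.80 in both arms: 6% − 2% = 4 points.

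**5. Correct attribution does not remove the problem.** Section 2 states that cooling reduces skin blood flow. A reaction may truly be caused by the vaccine and still be more or less frequent on cooled skin. Only a count made regardless of cause, by arm, would show that.

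**The case against.** The strongest reply is that 8.5 leaves out only events *clearly* due to immunization. If a reaction at the shared site cannot be cleanly assigned, it is not clearly due to the vaccine and stays in. Note *5 supports this: it collects events for which a TAK-01 cause cannot be ruled out, over the same period. Serious events are reported regardless. The exception also has an evident purpose: every child was to be vaccinated anyway, and injection pain is the efficacy outcome, so counting pain and crying as adverse events would partly duplicate FLACC.

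Much of this stands. A reader might infer that every event staff ascribe to the vaccine is lost, or that the arm comparison is biased in a known direction. The documents support neither reading. The wording is narrower, ambiguous reactions have a second route in, and the direction depends on attribution habits that nothing in the protocol reveals. The safety analysis is also descriptive, with no between-arm test stated.

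Three things remain. The conflict with 10.1, note *4 and 8.6 is explicit however narrowly 8.5 is read. Note *5 rests on the same judgement: an event called clearly due to the vaccine is one for which the device has, in effect, been ruled out. And the concern about duplicating FLACC justifies a rule for pain and crying, not a general exception by cause.

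**Conclusion.** The point holds as a contradiction in the data-capture rules and a risk to one secondary endpoint. Section 8.5 makes adverse event incidence depend on a causality judgement that 10.1 says is irrelevant, at skin that is both cooled or pressed and injected, probably by staff who know the arm.

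The size and direction of any distortion cannot be determined from the documents. The 4 to 20 points above rest wholly on assumed rates and exclusion shares, and a differential effect arises only if attribution differs by arm. Note *5 and 10.2.1 limit the loss, though local skin reactions would seldom meet the seriousness criteria in 10.2. The primary FLACC analysis is unaffected. The sponsor should correct this, but it does not threaten the trial's main conclusion.

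**What to change.** Reconcile 8.5 with 10.1, note *4 and 8.6:

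1. Delete the exception in 8.5. Record every event from the start of TAK-01 application to 10 minutes after inoculation, in both arms.
2. Record causality in two separate fields, one for the device and one for the vaccine, so that attribution describes an event rather than deciding whether it is recorded.
3. State that the expected injection pain and crying already captured by FLACC are not additionally counted as adverse events, by the same rule in both arms.
4. In 14.4.3, tabulate incidence by arm regardless of causality as the secondary endpoint, with device-related events as a subset.

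The cost is one more field on the case report form and a few more event lines, within a window that is already observed in a 60-child study. The protocol revision follows the route in section 15.
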